## Outcomes

The experimental design will be double blinded. The craving and VR cue reactivity will be recorded by three psychologists during the pre-test, two intervention sessions, as well as the post-tests at 1 day, 1 week, 1 month, and 6 months after the intervention.

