Thereafter, participants will be randomly assigned to one of four therapeutic groups using a randomization table generated by a sequence generator in a computer for matching. One group (R-10 min-E group) will receive R-E training, namely memory retrieval of methamphetamine-related cues in VR followed by extinction training after 10 min. Another group (NR-10 min-E group) will receive extinction intervention, namely memory retrieval of neutral cues in VR followed by extinction training after 10 min. The other group (R-6 h-E group) will receive R-E training outside the time window of 6 h, namely memory retrieval of methamphetamine-related cues in VR followed by extinction training after 6 h. The RV-10 min-E group will receive memory retrieval of methamphetamine-related cues in videos followed by extinction training after 10 min. Psychophysiological reactivity will be recorded instantaneously during the two times of intervention. The cue-elicited responses during the retrieval session will be assessed to indicate memory reactivation (28).

With the purpose of examining the effectiveness of R-E training in decreasing the spontaneous recovery of cue evoked responses, self-report craving and the VR cue reactivity assessment will be conducted at five different time points: pre-test, 1 day, 1 week, 1 month, and 6 months after the last intervention session. To measure the renewal effect, a new VR session with novel methamphetamine-related cues will be added to the VR cue reactivity assessment during the four post-tests compared to pre-test. Three psychotherapists with VR operation knowledge will conduct all the procedures for the four groups. The whole procedure of this study is depicted in a flow chart (**Figure 1**).

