### Intervention

All four groups will receive two intervention sessions over two consecutive days (19, 20). The intervention process will be conducted by one of three psychotherapists including a 3 min memory retrieval session and a 30 min extinction training session. Psychotherapists should have technical ability to operate VR (self-developed through the collaborative work of the psychotherapists and researchers) to ensure the treatment's consistency and fidelity. The content of the extinction training session will be the same for the four groups. However, the intervention processes of four groups will differ in the content of the memory retrieval session and the time point of implementing extinction training.

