#### NR-10 min-E Group

Participants will be provided with two intervention sessions for two days, both including 3 min of neutral cues retrieval followed by 30 min of extinction training 10 min after. The implementation of the retrieval session will guide participants to explore a neutral VR scene without methamphetamine-related cues. To ensure that the methamphetamine-associated memories of the participants will not be reactivated to a labile state, this session should be irrelevant to drug-associated stimuli.

The content of the extinction training session that the NR-10 min-E group will be exposed to is the same as the content that the other three groups will be exposed to.

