#### R-6 h-E Group

Participants will receive two intervention sessions that the content of the retrieval session and the extinction training session will be identical to the R-10 min-E group. The only difference is that extinction training will be conducted 6 h after memory retrieval, when methamphetamine-associated memories are supposed to be reconsolidated again.

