#### RV-10 min-E Group

Participants will receive two intervention sessions for two successive days. The duration and the time interval to implement the intervention sessions of the RV-10 min-E group are the same with the R-10 min-E group and the NR-10 min-E group. However, the method to present methamphetamine-associated cues of the RV-10 min-E group in the retrieval session is different from the other three groups. The participants will watch a video related to methamphetamine lasts 3 min to retrieve drug-associated memories. 10 min after the retrieval session, a same extinction training session will be implemented.

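### The article calls the design double blinded, but the staff who deliver the arms and record outcomes in the sessions must see the allocation, and participants can perceive their own procedure

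*Protocol article*

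**What the plan says.** The blinding statement is one sentence in the Outcomes section: "The experimental design will be double blinded". The next sentence names the recorders: "The craving and VR cue reactivity will be recorded by three psychologists during the pre-test, two intervention sessions, as well as the post-tests".

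Study Procedure uses a different role name: "Three psychotherapists with VR operation knowledge will conduct all the procedures for the four groups". The Intervention section repeats it for delivery: "The intervention process will be conducted by one of three psychotherapists including a 3 min memory retrieval session and a 30 min extinction training session".

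On how the arms differ, the Intervention section says that "the intervention processes of four groups will differ in the content of the memory retrieval session and the time point of implementing extinction training", while extinction content is common to all four. The arm descriptions fill this in:

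- NR-10 min-E: "The implementation of the retrieval session will guide participants to explore a neutral VR scene without methamphetamine-related cues".
- R-6 h-E, relative to R-10 min-E: "The only difference is that extinction training will be conducted 6 h after memory retrieval".
- RV-10 min-E: "The participants will watch a video related to methamphetamine lasts 3 min to retrieve drug-associated memories".

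Primary Outcomes lists self-reported craving on a 0–100 visual analog scale, together with the psychophysiological recordings.

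**The concern.** Double blinding is a specific claim about protection against bias, and readers will weigh the results by it. Here the features that reveal the arm are the experimental manipulations themselves: drug or neutral cues, VR or video, short or long delay. A fuller protocol could add detail on who is masked, but it could not make these features invisible to the person running the session.

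The claim is attached to a self-rated primary outcome. If participants form different expectations in different arms, or if staff who know the arm handle the post-tests differently, craving ratings can shift without any effect on the drug memory. The Discussion hopes for compelling evidence from this trial. Presenting the result as double blind would lead readers to underrate the risk of bias.

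**Working it through.** No calculation underlies this point. The check takes each party in turn and asks whether the article's own description lets that party be blind.

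1. **Staff who deliver the arms.** One of three psychotherapists runs retrieval and extinction (Intervention). That person has to start a drug scene, a neutral scene or a video, and has to schedule extinction after 10 min or 6 h. Doing so requires knowing the arm. *Not blind.*

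2. **Staff who record the outcomes.** There are two readings.
   - If the psychologists in Outcomes are the psychotherapists in Study Procedure, they deliver the arms and step 1 applies.
   - If they are other people, Outcomes still places them in both intervention sessions, where retrieval content and delay are in view.

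   On either reading, *the recorders are not blind as described*. The article leaves open which reading is meant. The sentence giving the psychotherapists all procedures directly follows the description of the five assessments, so it can be read as covering the post-tests, but it does not name them.

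3. **Participants.** Each participant knows whether drug cues or a neutral room were shown, whether retrieval was in a headset or on video, and whether the wait was 10 min or 6 h. The researcher also explains the procedure before consent (Study Procedure). No masking device or sham wait is described. Participants are *not blind to their own procedure*. They may still be unaware of which procedure is expected to work better, but the article does not say that this is ensured.

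4. **Outcomes exposed.** Craving is rated by the participant, using the VR controllers (Apparatus, Primary Outcomes). It is open to expectancy through step 3. Heart rate, skin conductance and EEG are instrument recordings, so they are less open to it, though their processing still involves choices that someone aware of the arm could influence.

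5. **Effect on the sample size.** The stated total reproduces: 4 × 20 = 80, and 80 / (1 − 0.15) = 94.1, rounded up to 95. Nothing in this calculation depends on blinding, so correcting the description leaves 95 unchanged.

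**The case against.** The strongest reply is that perceiving one's own procedure is not the same as knowing one's allocation. Each participant meets one arm only, every comparator is active, and all receive the same extinction training. Someone who waits 6 h has no stated reason to think 10 min is better. The article does not say that all four arms or the hypothesis are disclosed at consent, and the consent material is not available here. This stands. A reader might infer that participants have no protection at all against expectancy, and the documents do not support that. They also do not support the claim made, since hypothesis-unawareness is weaker than blinding and is not stated.

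Three further points limit the finding:

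- A reader might take it as settled that the treating psychotherapists run every post-test. Outcomes names psychologists as recorders, so this is unresolved. What defeats recorder blinding is their presence in the intervention sessions.
- A reader might treat craving as the only primary outcome. Psychophysiological recordings are listed beside it. Participants also enter their own ratings, which limits assessor influence on the score.
- A reader might want a figure for the bias, or a ranking of the contrasts by exposure. Only a shift that differs between arms biases a contrast, and the article supplies neither such a shift nor an SD. It also gives no basis for calling one contrast more exposed than another.

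It can also be said that full masking is rarely possible in behavioural trials and that a condensed article leaves details of masking to the full protocol. Both are fair. They excuse the absence of blinding and of detail, but not a flat statement that the design has a property its own procedures exclude.

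**Conclusion.** The double-blind claim does not hold as written. Delivering staff must know the arm, and recorders sit in sessions that reveal it. Participants can perceive their own procedure and are at most unaware of the hypothesis. This rests on the article's descriptions of the arms and staff roles and needs no assumption about whether psychologists and psychotherapists are the same people.

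No numerical size can be given for the bias from these documents. Qualitatively, self-reported craving is the most exposed and the instrument recordings less so. Design and sample size are untouched. The correction is nevertheless necessary, because the article asserts a protection that the trial lacks and does so for a self-rated primary outcome.

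**What to change.** - In Outcomes, replace the double-blind statement with one saying that treating staff are not blinded and that participants are not blinded to their procedure. Add that participants are unaware of the hypothesis only if this is ensured.
- Reconcile Study Procedure, Intervention and Outcomes on who delivers the sessions and who records and assesses.
- Where staffing at the Changsha and Foshan sites allows, have each participant's post-tests run with scripted instructions by an existing staff member who neither delivered nor recorded that participant's sessions. Claim blinded assessment only if this is done.
- Process the heart rate, skin conductance and EEG data, and run the analysis, under coded arm labels.
- In the conclusions, describe craving as a self-report obtained without double blinding.

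**Cost.** The wording and the coded labels are cheap. The post-test arrangement adds a small scheduling burden. With three psychotherapists named and two sites in different provinces, it may not be feasible for every participant, which is why it is conditional. The remaining downside is a less favourable blinding description.

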### Primary Outcomes

Self-report craving for methamphetamine will be measured using a 100-point visual analog scale in VR ranging from 0 (no craving) to 100 (high craving).Psychophysiological recordings (see below for details) will be carried out at every VR cue exposure including two intervention sessions and VR cue reactivity assessments at the pre-test and the 1 day, 1 week, 1 month, and 6-month follow-ups.

### Secondary Outcomes

Anxiety will be measured with State-Trait Anxiety Inventory (STAI) (32). STAI is a widely used scale for general anxiety (33, 34). Chronic methamphetamine use may cause emotional dysfunction including anxiety (29). The Chinese version of STAI is a 20-item self-report instrument with a satisfying internal consistency (Cronbach's alpha = 0. 88) (35) and scores from 20 (absence of anxiety) to 80 (high anxiety).Dropout rate will be assessed to indicate the motivation of participants to effectively engage in the treatment program (36, 37). Many methamphetamine users are reluctant to enter treatment and once in treatment there is an unacceptably high early dropout rate (38). Dropout rate is an important indicator may reflect the acceptability of the MUD treatments. The number of participants will be recorded at different time points for calculating the dropout rate.

### Psychophysiological Outcomes

Heart rate (HR) and heart rate variability (HRV) will be evaluated with the Biopac 16 Physiological multichannel instrument (BIOPAC MP150) during VR cue exposure at pre-test, two intervention sessions and four post-tests. HR reflecting the average heart rate is a kind of automatic response to emotional arousal. HR increases during anxiety states and decreases during relaxed states (39). As one of the main indicators of cue reactivity, the HR in individuals with SUDs may increase when they are exposed to drug-associated cues (5). The HRV indicates the fluctuations in HR around an average HR (30), which decreases during an anxious and exciting state and increases during a relaxed and calm state (39). HRV is also used as an autonomic index of emotion regulation capabilities (40), responding sensitively to drug-associated cues (41). HR and HRV are frequently regarded as objective measurements of anxiety responses and craving reactivity (5).Skin conductance reactivity (SCR) will be recorded at the same time as the HR using BIOPAC MP150. Two Ag/AgCl electrodes of 20 mm×16 mm will be attached to the medial phalanges of the first and third fingers of the non-preferred hand of participants to obtain the signal of SCR. SCR is affected by emotional arousal, finger temperature, and finger activity. For recording SCR stably, participants will be told to keep the non-preferred hand down when they are exploring the VR scenes. SCR is considered to be an important index for cue reactivity evoked by drug-associated cues (30). During the state of craving, the blood vessels and sweat glands may change which will cause changes in the skin resistance, resulting in changes of the skin electricity. The spontaneous changes of SCR may be caused by R-E training, as demonstrated by a previous study (22). SCR has been used to measure craving in a previous methamphetamine study (42).Electroencephalogram (EEG) will be recorded using an application of a mobile EEG equipment at the same time as the HR and the SCR. Four channels (TP9, FP1, FP3, TP10) will be kept to measure brain waves including alpha, beta, delta, and gamma frequencies. Previous studies on SUDs revealed that drug-associated cues evoked pronounced EEG power spectrum (43). The EEG has been used in previous studies as an objective index of cue reactivity to show craving (44).

## Sample Size

ANOVA was used to calculate the sample size (power = 80%, α = 5%). The calculation was based on the relevant data of a previous study of R-E training for individuals with tobacco use disorder, whose main results related to cue-elicited craving and reactivity (reference point =20%) (20). The result indicated that a minimum of 20 participants per group will be required for subsequent analysis. Taking into consideration that 15% of the participants may potentially drop out from the study, 95 eligible participants are needed for inclusion.

## Statistical Analysis

The means, medians, standard deviations, and ranges of the data will be summarized for quantitative data and counts and frequencies for categorical data. Primary outcomes and secondary outcomes will be analyzed separately. ANOVA (quantitative variables), Manna-Whitney-Wilcoxon test (ordinal variables), or Chi-square test (frequencies) will be used to compare outcomes between groups at baseline. Non-parametric tests will be used for data that are not normally distributed. Multiple imputations will be used to address the missing data if necessary. Furthermore, the mixed linear model analysis will be applied to compare outcomes among groups at follow-up assessments. Statistical significance is defined as p ≤ 0.05. Statistical analyses will be performed using SPSS statistics software, version 19.0 (SPSS Inc., Chicago, IL, USA).

## Discussion

To our knowledge, this study is the first intending to evaluate the effects of R-E training combined with VR on reducing methamphetamine-related craving and cue reactivity clinically. The primary findings of the randomized controlled trial may suggest that R-E training delivered by immersive VR may be highly effective for the reduction of craving and reactivity evoked by drug-associated stimuli in comparison to extinction and may ultimately decrease the rate of relapse. Another important point of the proposed study may be that using VR is more effective than using traditional methods to implement the memory retrieval during the reconsolidation intervention in decreasing cue-induced responses. This may provide the first proof that VR may improve the effects of the reactivation of drug-associated memories during R-E training.

First, this study pays close attention to MUD. In China, MUD constitute the majority of SUDs, especially among the youth (1, 2). Methamphetamine is a highly addictive psychostimulant drug that induces psychological dependence and has serious effects on mental health, posing a treatment challenge (45). Relapse is one of the main clinical problems in the treatment of SUDs (46), especially MUD, suggesting that more effective strategies are needed for relapse prevention in MUD.

Drug-associated memories may be the main factor of relapse in MUD. R-E training is expected to decrease cue-evoked craving and reactivity through a single reminder exposure to reactivate drug-associated memories prior to extinction training. A previous study showed that R-E training decreased conditioned fear response which was stubborn in case of spontaneous recovery, renewal (17). Furthermore, the findings of animal and human laboratory studies on conditioned fear are consistent with the reconsolidation hypothesis (18, 47, 48). As far as we know, the clinical utility of R-E training in SUDs has been examined in only two previously published studies. One study was about heroin use disorder, which found a marked reduction in self-report craving 6 months after R-E training, when compared to extinction or R-E training provided outside the time window of 6 h (19). The other one, which concerned nicotine use disorder, showed that using R-E training reduced drug craving elicited by novel drug-associated cues (20). These studies revealed significant clinical benefits of R-E training for inhibiting spontaneous recovery or renewal of cue-evoked craving and reactivity when compared to control groups. The consistent outcomes support the notion that the reactivation of drug-associated memories may be essential for disrupting the reconsolidation of original drug-associated memories by incorporating new information (extinction training) (16). Thus, the present study shares the same opinion with Xue et al. and Germeroth et al. on R-E training reducing spontaneous recovery and renewal of drug craving in SUDs. The effects of R-10 min-E training, NR-10 min-E training, and R-6 h-E training will be compared at 1 day, 1 week, 1 month, and 6-month follow-ups to test for the spontaneous recovery effect after the two intervention sessions, in the meanwhile, craving and reactivity elicited by novel methamphetamine-related cues will be assessed to test the renewal effect. Translational researches on R-E training may help people better understand the mechanism and process of memory reconsolidation. Also, clinical studies provide a new perspective on the treatment of SUDs (49).

Yet, there are still several inconsistent results about the effects of R-E training in some memory studies on conditioned fear (21, 22, 50, 51) or SUDs (52, 53), that may be due to the methodological differences (54) and inter individual differences between studies (55–57), which may result in limited reactivation of previously consolidated memories. From a theoretical perspective, VR appears to be a more useful method to reactivate drug-associated memories as drug-associated cues in VR elicit more stronger craving than drug-associated cues in pictures (24) or videos (25, 26). Using VR can not only present drug-related paraphernalia in proximal confrontation patterns, but also provide interaction with specific drug-related environment or multi-sensorial stimuli (distal risks), which are known to be the most critical triggers of relapse (58, 59). VR might thus offer high-risk methamphetamine-related environments. Then, the methamphetamine-related memories of participants may be reactivated to a labile, modifiable state more probably. To test this inference, the intervention effectiveness of the R-10 min-E group and the RV-10 min-E group in reducing cue-elicited responses will be compared in the present study. VR may be examined to promote the reactivation of drug-associated memories providing the intervention effectiveness is better through using VR to present drug-associated cues than using videos in the retrieval session. On the other hand, VR combined with extinction training may mitigate methamphetamine-related craving or extinguish cue reactivity. It is consistent with a previous study that VR combined with cue exposure treatment made progress in treating nicotine use disorder (60). Through this novel method, the relapse of people with MUD would be in good control when facing similar environments in reality.

There are several limitations to this study protocol. First, considering the feasibility and applicability of the study, the duration of exploring VR may cause discomfort due to the weight of the headset. Second, although VR scenes have been validated to be almost the same as the environments in which participants usually use methamphetamine, it is possible that a proportion of the participants may be unfamiliar with these situations, and therefore they may respond to new stimuli other than methamphetamine-related cues. Third, social interactions (with avatars in VR) are not included in these VR scenes. Future researches should consider employing more diverse designs involving social and personal drug-associated cues or triggers for dynamic plots (e.g., striking a light for methamphetamine or producing smoke) for VR scenes. In addition, there is no exact index to measure the extent of reactivation for drug-associated memories objectively. In this study or future studies, some psychophysiological measures combined with subjectivity experience may be regarded as a reference for the extent of reactivation. More important, as the participants will maintain the abstinence status in the rehabilitation centers when the study protocol are implemented, they will have no access to using methamphetamine that will make some objective measurements to test relapse rate infeasible, such as the urine test and hair test. These tests may be implemented after the participants get out of the rehabilitation centers to confirm the intervention effectiveness in the future.

The present study may extend the efficacy of R-E training on drug-associated memories by combining VR with R-E training to decrease cue-elicited craving and reactivity in people with MUD. The findings of the study may provide initial, compelling evidence that a brief R-E training in VR can attenuate methamphetamine-related craving and cue reactivity, which will have significant implications for relapse prevention and future studies on memory reconsolidation. VR will potentially become a maneuverable and low-cost approach for presenting controlled, individualized, and ecologically valid high-risk situations to people with SUDs receiving treatments. Ultimately, R-E training combined with VR may be a promising treatment for people with SUDs to prevent relapse.

